					**Mths after birth years**					
Neonatal Brazelton Assessment Scale (NBAS)	Neonatal behavior (0–1 month)	Brazelton e (58) (3° ed)	Psychologist at the maternity hospital/home visit	The assessment concerns: autonomic system motor tone organization state organization and regulation early interaction	X				X	X
Brunet-Lézine Revised Developmental test	Child development (2–30 months)	Brunet and Lézine, 1965 (59)	Psychologist during home visits	Developmental age (developmental quotient)4 dimensions: Language Social relationships Motor gross Motor fine 30 item test scored partly		X	X		X	X
Alarm Baby Distress scale (ADBB)	Sustained withdrawal behavior (2–24 months)	Original scale in FrenchGuedeney and Fermanian (60) in France	Psychologist, after home visits, with video	8 items, 5 point Likert scale (0–4), range 0–32 Withdrawal behavior if ≥ 5		X	X		X	X
Symptom Check-list (SCL-90)	Mother's psychological disorders	Derogatis (61) Translation	Mother during home visits	90 items, 5 point-Likert scales (0–4) X X X10 subscales: Somatization (0–48) Obsessive-Compulsive (0–40) Interpersonal Sensitivity (0–36) Depression (0–52) Anxiety (0–40) Hostility (0–24) Phobic Anxiety (0–32) Paranoid Ideation (0–24) Psychoticism (0–40) Other symptoms (0–28) Higher scores indicate greater Clinical impairment.		X	X		X	X
Working Alliance Inventory (WAI)	Working alliance between the mother and the pediatric nurse	Horvath and Greenberg (62) French validation Guedeney et al. (63)	Mother and pediatric nurse after home visits	12 items, Likert scale (1–7) Range 12–84 Higher scores indicates better working alliance		X	X		X	
Attachment Q-Sort (AQS)	Child's attachment (10 months−3 years)	Waters and Deane (64) French translation made and validated by a panel of infant mental health experts (65)	Assessment team (psychologist and nurse) after home visits	Two rates assess each situation during a home visit of 2 h90 itemsCorrelation with typical secure pattern: Insecure attachment if <0.35 Secure attachment if ≥ 0.35			X		X	X
Edinburgh Postnatal Depression Scale (EPDS)	Self-Assessment of postpartum depression	Cox et al. (66) French validation: Guedeney and Fermanian (67)	Mother during home visits	10 items, 4 point-Likert scales (0–3) Range 0–30 Higher scores indicate higher levels of depressive symptoms.		X			X	X
Bobigny's early interactions grid	Mother-infant interactions (0–4 years)	Devised by experts in infant mental health and specifically perinatal consultations, 1989 (68)	Psychologist after home visits	Qualitative assessment grid describing the quality of the interactions and the dominant mode of interaction.		X	X		X	X
Mini Q-SORT	Maternal sensitivity	Pederson and Moran (69) Suited to analysis of short video sequences Tarabulsy and et al. (70)	Psychologist after home visits (video)	Sorting of 25 cards describing maternal behavior according to a Q-sort procedure		X	X		X	X
Beck Depression Inventory (BDI)	Maternal depression	Validated by Beck et al. in 1961 (71) Version abridged by Beck et al. in 72 (72) Translated and validated in French by Delay and Pichot in 1963 and 1964 (73, 74) Abridged version validated by Reynolds and Gould et al. in 1981 (75)	Mother during home visits	13 items 4-point Likert scales Range 0–39 Higher scores indicate higher levels of depressive symptoms. 4: no depression; 4–7: mild depression; 8–15: moderate depression; 16+: severe depression			X		X	X
Family Affluence Scale (FAS) form	Socio-economic status of the families		Mother during home visits	4 questions to tick: yes/no and enter number		X	X		X	X
Brief Infant-Toddler Social and Emotional Assessment (BITSEA)	Early screening for delays in social and emotional competencies (1–3 years)	Validated by Briggs-Gowan and Carter and (76) Translated by Wendland and Saïs, 2010 and validated in French by Wendland et al. (77)	Mother during home visits	42-item questionnaire 3-point Likert scales (0–2) Provides indications on the social-emotional profile and competencies of children according to their parents.			X		X	X
Parenting representations interview (PRI)	To obtain parents' representations concerning their child, themselves as parents and their experience of the intervention	Questions taken from the R interview drawn up by Lebovici et al. (78)	Mother during home visits	Semi-structured interview 4 questions. The themes are: description of their child, themselves as parents, their reaction to their child's crying, and their experience of the support and home intervention as part of the research		X	X		X	X
Language delay screening test (ERTL 4)	To assess language delays at age 4 years	French scale validated in 1998 (79)	The pediatric nurse during a systematic examination at nursery school	5 tests (2 optional), scoring with 3 categories: red (indication of further testing); orange (active monitoring, re-evaluation necessary); green (no difficulty)				X	X	X

Assessment of any language delay is undertaken in all schools in France by the PMI service, during the second year of kindergarten (at 4 years old).

If disorder or delay is observed in the child or the parent (such as postpartum depression, depressive symptoms, development or language delay, conjugopathy, addiction, etc.) then parents in the control group who are encountered at 4- and 24-month evaluations are referred to specialist services. For the intervention group, the evaluation HV process is identical. For this group should a delay in the child or parental mental disorders be noted by the PMI nurse then the family is immediately referred to a specialist service while remaining in the PERL system. SB is also informed in order to note the orientations carried out within the framework of the mechanism.

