##### Evaluation in Both Groups

To check the initial homogeneity of the groups, we proposed an early comparison of the groups with 10 families from each group, randomly selected by a double-blind process. An independent psychologist assessed the baby's development during the first 30 days after birth.

Two HVs are carried out by SB (and the family's dedicated PMI nurse in the “intervention” group), with the parents, taking place when the child is 4 and 24 months old. The purpose is to assess three things: the child's development, parenting, and parent-child interaction. The assessment tools are described in Table 3.

**Table 3 T3:** Outcome criteria and assessment schedule.

**Instrument**	**Concept measured**	**Validation**	**Outcome assessment place of evaluation**	**Structure of instrument; scoring**	**Time of measurement**				**Group**	
					**0**	**4**	**24**	**4**	**I**	**T**

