Family recruitment was completed in December 2019. The fourth month evaluations were completed in July 2020, and 24-month evaluations are currently underway. The first results will be analyzed in 2021, examining the characteristics of the study population, homogeneity of the groups, and the scores on the tests at 4 months. The comparative analysis will begin in 2022, once the 24-month evaluations are completed for both groups. The final comparative analysis will be carried out in 2024–2025, when all the 4 ERTL tests have been carried out by the PMI nurses.

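### The family's own nurse attends the evaluation visits in the intervention arm only, and the article contradicts itself on who rates attachment, so the AQS and the maternal self-reports are not set up alike in the two arms

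*Protocol article*

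**What the plan says.** **Attendance.** Evaluation in Both Groups says that the coordinating psychologist carries out the evaluation visits, joined by a nurse in one arm: "and the family's dedicated PMI nurse in the “intervention” group), with the parents, taking place when the child is 4 and 24 months old".

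**Attachment.** Table 3 schedules the AQS at 24 months for both groups. The rater is "Assessment team (psychologist and nurse) after home visits", and the scoring column adds "Two rates assess each situation during a home visit of 2 h". The result is dichotomised: "Insecure attachment if <0.35 Secure attachment if ≥ 0.35".

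**Self-report.** For the SCL-90, EPDS, BDI and BITSEA, Table 3 gives the source as "Mother during home visits". The Working Alliance Inventory, by contrast, is completed after the visits, so the table does distinguish the two settings.

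**Statements that point the other way.** The text after Table 3 says that the evaluation visit follows the same process in the intervention group. Strengths and Limitations lists the AQS among the video-based tests to be scored blind by the coordinator and other psychologists.

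**Language at 4 years.** Table 3 assigns the ERTL-4, in both groups, to "The pediatric nurse during a systematic examination at nursery school". Clinical and Research Implications times the final analysis for "when all the 4 ERTL tests have been carried out by the PMI nurses". Strengths and Limitations notes that most PMI nurses in the area take part in PERL.

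**The concern.** Attachment and maternal mental health are named hypotheses. If the person who delivered the intervention is at the assessment in one arm and not in the other, any effect of her presence or of her ratings coincides completely with treatment. No adjustment in the analysis can separate the two, and a blinded analyst cannot undo a difference that arose when the data were collected. The limitations section discusses the coordinator's several roles but not the nurse's attendance.

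The ERTL-4 raises a different question. Language delay is part of the main objective, no blinding is stated for this test, and nothing in the article stops a PERL nurse from testing a child whose family she has visited for four years.

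**Working it through.** **1. The passages side by side**

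| Item | Intervention arm | Control arm | Where |
|---|---|---|---|
| Present at 4- and 24-month visits | Coordinating psychologist and the family's own nurse | Coordinating psychologist; no nurse named | Evaluation in Both Groups |
| AQS raters | Psychologist and nurse | Psychologist and nurse | Table 3 |
| AQS scoring | Blind, from video, by psychologists | Same | Strengths and Limitations |
| Evaluation process | Said to be the same as in controls | – | Text after Table 3 |
| Self-reports | At a visit attended by the nurse | At a visit with no nurse named | Table 3 with Evaluation in Both Groups |
| ERTL-4 | PMI nurse at school | PMI nurse at school | Table 3 |

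The first three rows cannot all hold. If Table 3 governs, the control arm lacks a defined second rater. If Strengths and Limitations governs, the rater entry in Table 3 is wrong. Even then, one named blind scorer is the coordinator, who performed the randomisation (Sample Characteristics) and conducts the visits.

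**2. The plan's own sample size**

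Determination of Sample Size uses 50% against 25% developmental delay, alpha 5%, power 80% and 1:1 allocation. Taking the test as two-sided, with pooled variance under the null and no continuity correction:

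n = [1.96 × √(2 × 0.375 × 0.625) + 0.8416 × √(0.50 × 0.50 + 0.25 × 0.75)]² / 0.25²
= [1.342 + 0.557]² / 0.0625 ≈ 57.7, so 58 per arm.

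The stated 58 is reproduced. It is used below only as the number analysed per arm.

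**3. What a shift in one arm would do (illustration)**

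The documents give no size for a rater or setting effect, so the shifts are assumptions. There is no true effect, and the test is two-sided at 5%.

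*Continuous score.* SE of a standardised difference = √(2/58) = 0.186. False-positive rate = Φ(b/SE − 1.96) + Φ(−b/SE − 1.96).

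| Assumed shift b (SD) | b/SE | False-positive rate |
|---|---|---|
| 0 | 0 | 5% |
| 0.1 | 0.54 | 8% |
| 0.2 | 1.08 | 19% |
| 0.3 | 1.62 | 37% |

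*Secure/insecure AQS classification.* Assume a base rate p of 40% to 60% secure and a shift b in the intervention arm only. With p̄ = p + b/2, SE₀ = √(2p̄(1 − p̄)/58) and SE₁ = √([p(1 − p) + (p + b)(1 − p − b)]/58), the rate is Φ((b − 1.96 SE₀)/SE₁) + Φ((−b − 1.96 SE₀)/SE₁). For p = 50% and b = 10 points, SE₀ = 0.0924 and SE₁ = 0.0919, which gives 19%.

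| Assumed shift | False-positive rate, p from 40% to 60% |
|---|---|
| 5 points | 8–9% |
| 10 points | 19–20% |
| 15 points | 37–41% |

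**4. Reach of the problem**

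Table 3 has a psychologist give the Brunet-Lézine test, and Strengths and Limitations lists it for blind analysis. The rater conflict therefore does not reach the outcome that sized the trial, although the nurse attends that visit too. For the ERTL-4, only the 64 intervention families have a PERL visitor, so at most those 64 children could be tested by their own visitor.

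**The case against.** The case on the other side has weight in several places.

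- **The AQS may be blind after all.** If the statement in Strengths and Limitations governs, psychologists score it from video in both arms and the difference in raters disappears. That is possible, but Table 3 says otherwise, and the article does not say which holds.
- **The treating nurse as AQS rater is an inference.** Table 3 does not say which nurse rates. She is the only nurse named at any evaluation visit, so the inference is strong, but it remains one.
- **Nobody says that the nurse watches the mother answer.** She attends the visit, and the article is silent on how the forms are handed out. The setting differs by arm. How closely she is involved is unknown.
- **The direction is not established.** A reader might infer that the bias favours the intervention. The article describes the nurse as a secure figure for the parent, so mothers might equally disclose more symptoms in her presence.
- **Unmasking through video is not shown.** A reader might suppose that the nurse on camera reveals the arm. No passage says that she is filmed. Keeping her out of frame is only a precaution.
- **The ERTL-4 is not measured differently by design.** A reader might infer that nurses rate it in the intervention arm only, or that all 128 results are exposed. Neither is supported: the test, the service and the school occasion are the same in both arms. What remains is an assessor with no stated blinding, who for some intervention children may be the family's own nurse.

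**Conclusion.** The concern holds in a limited form. It is explicit that the treating nurse attends the evaluation visits in one arm only. Read with Table 3, this leaves the AQS raters either different by arm or undefined for controls, and it places maternal self-reports in different settings. Both conflict with the claim of a common process, and the AQS entry conflicts with the claim of blind video scoring.

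The outcomes affected are secondary. The size of any bias is unknown and its direction uncertain. The 19% at 0.2 SD rests on an assumed shift and on 58 analysed per arm, and shows only that a modest difference in measurement would matter in a trial of this size. The ERTL-4 is a separate and smaller point about unblinded assessment. The passages should be reconciled before the comparative analysis.

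**What to change.** 1. **Reconcile the AQS passages** (Evaluation in Both Groups, Table 3 and the text after it, Strengths and Limitations). Base the between-arm comparison only on sorts made from video by psychologists who did not attend the visit and do not know the arm, by the same procedure in both arms. This excludes the coordinator as a scorer for this comparison. Use any nurse sort descriptively. Table 3 refers to a two-hour visit, so state how much of it the recordings cover.
2. **Remaining 24-month visits.** Have mothers complete the SCL-90, BDI and BITSEA away from the nurse, and keep the nurse out of filmed sequences. The EPDS is given only at 4 months, and those evaluations were completed in July 2020, so it can no longer be changed.
3. **Assessments already done.** Report as a limitation that they were nurse-attended in one arm only. Repeating the analysis without nurse-attended assessments would not help: it would remove intervention families and no controls.
4. **ERTL-4.** Where the existing rota allows, an intervention child should not be tested by the nurse who visited that family. Record any test that the family's own nurse does give.

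The cost is a wording change and some rescheduling among existing staff, since other psychologists are already named as video scorers. The nurse has a smaller role at the joint evaluation visit, and some school sessions are swapped. The swaps may not always be feasible across an area of 178 towns with nurses who do PERL on top of their normal work, hence the condition in item 4.

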#### Accompaniment for PMI Nurses

##### Supervision: Systemized and *ad-hoc*

The PERL study's PMI nurses receive monthly supervision from a child psychologist and SB.

PMI nurses can contact SB at any time to report any difficulties encountered with the families. Individual supervision is also offered on request.

In the PERL study these supervisions sustain the unconditional kindness and necessary framework, and so are essential in support of the families (80, 81).

##### Training

All PMI nurses received initial training on the fundamental principles of support relationship and the factors that facilitate or inhibit it; the fundamental components of perinatal support; the “echo function”; and the principles of communication, attachment, therapeutic alliance, and their variations. There is also ongoing education to ensure awareness of rating scales, analysis of videos based on interaction and the baby's sustained withdrawal behavior, theoretical contributions about play, attachment, postpartum depression, unconditional kindness, and the non-directive-approach, the place of advice and guidance in the HVs, etc.

##### Working and Exchange Days

The PMI nurses attend quarterly working and exchange days where they review their roles and undertake 1 h a month of continued training.

The theoretical model proposed in this research program is intended to be eclectic: the fundamental principle of therapy described by Rogers (82), systemic and family theory (56, 83–85), free drivability (86), attachment theory (39, 87, 88), mother-baby therapies developed by Fraiberg (12) and Dolto (89, 90), etc., to offer PMI nurses a range of practices and interventions for use with the families. This model will be enhanced over the course of the meetings between the PMI nurses and SB, in line with their expectations.

PMI nurses who join the program during the assessment have an interview with SB at which time the details of the trial are explained and the model and content of the HVs of the intervention group are presented.

### Data Collection

The data are collected by SB during the child's fourth and 24th month and HVs and stored at the CPN under conditions guaranteeing confidentiality. Personal data are stored in separate places.

All the details regarding people leaving the trial (lost to follow-up, refusal to continue with the research, child taken into care, etc.) will be recorded for analysis. For the intervention group, data is collected by PMI nurses during HVs, or by SB if the fourth month HV is accessible (family setting, professional situation, daycare arrangements, etc.). For the control group, the same data will be accessible if they have not withdrawn prior to the fourth month visit. If a family leaves the study before the HV at 4 months, SB will attempt to contact this family to obtain this information. If the information cannot be obtained, SB will only have access to the information recorded in the pregnancy notification, which includes the number of dependent children, the mother's age, address, child's date of birth, and PMI follow-up.

For families not wishing to join the research program, the known data, such as address, number of dependent children, and mother's age, will be recorded for analysis to compare consenting families with non-consenting.

If the protocol is not followed, i.e., HVs are not carried out, the dedicated PMI nurse calls the family three times. Should the family not respond, SB phones the family to attempt to understand why parents wish to withdraw from the study. SB may propose adjustments (change of PMI nurse or modification to the HV timetables). If the family maintains its position, the family will be withdrawn from the protocol and their details studied. In addition, the family may still benefit from the usual follow by the PMI nurse if necessary.

During the semi-directed interview at 4 and 24 months, SB establishes whether the families receive similar follow-up (psychologist, psychiatrist, PMI visits, social workers, speech therapist, etc.) in order to analyze these data and link them to the results obtained in assessments.

We have chosen to conduct most assessments at 24 months to meet the primary objective and to limit the number of families lost to follow-up.

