**Figure 2 F2:**
[figure not shown]
Study design of the PERL study.

These HVs take place at predefined intervals (1 HV every month from birth up to the child's 1st birthday, 1 HV every 2 months from 1 to 2 years of age, and 1 HV every 3 months from 2 to 4 years of age) as shown in Figure 2, totaling 26 HVs over 4 years.

The work of PMI nurses is focused on unconditional kindness and availability, enhancing parenting skills, non-directive action, responsiveness to parents' needs and questions, parental contact and support, having a positive approach to situations, and the building of a secure parent/pediatric nurse relationship.

*Particular Case*. Intervention concerns all families residing in the area targeted by the study (universally), irrespective of the make-up of the family (nuclear or single-parent families). Support and assessment will be provided under the same conditions for a single-parent.

At the inclusion stage, the smallest child of the family is included. If during the study a birth should occur in the family, the study will continue without the inclusion of the newborn. Only 1 child in the family is assessed, from birth (4 months) to 4 years.

If other children are present (physically or in conversation), the PMI nurse can meet them: the goal is to respond to parents' requests and to support them throughout their parenthood.

Should the father wish to be present during the HV, they are welcome to do so. Other parents are able to attend HVs should the mother be unavailable; however, the evaluation focuses only on the mother to ensure comparability of certain gender-sensitive tests.

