##### Control Group

There is no specific intervention for families in this group, with the exception of the recruitment HV carried out by SB and the two evaluations planned in the study.

While a family in the control group can benefit from monitoring systems should they need to do so (midwife, conventional PMI consultations, maternity hospital, psychological medical center, social worker, and pediatrician, etc.), this is not specifically proposed through the PERL study.

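### A family that keeps refusing nurse visits is withdrawn from the whole study, with no stated way to stop visits and keep the 24-month evaluation; this route out exists in the intervention arm only

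*Protocol article*

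**What the plan says.** The rule stands in the Data Collection section of the protocol article. It starts from missed programme visits: "If the protocol is not followed, i.e., HVs are not carried out, the dedicated PMI nurse calls the family three times". If the family does not answer, the coordinating psychologist phones to learn why the parents want to leave the study. The remedies named concern the visits only: "SB may propose adjustments (change of PMI nurse or modification to the HV timetables". The end point is: "If the family maintains its position, the family will be withdrawn from the protocol and their details studied". The family may still receive ordinary PMI follow-up.

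The visits belong to one arm. The section on the intervention group's support schedules them, "totaling 26 HVs over 4 years". Evaluation in Both Groups mentions "the family's dedicated PMI nurse in the" intervention group only. For controls the text reads: "There is no specific intervention for families in this group, with the exception of the recruitment HV carried out by SB", plus the two evaluations.

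For families who leave, Data Collection provides for recording reasons and background information. It describes no further outcome assessment. The same section ties the 24-month assessments to the primary objective and to limiting loss to follow-up. The 4-year language screen works differently: "Assessment of any language delay is undertaken in all schools in France by the PMI service".

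**The concern.** Declining further nurse visits and declining to be evaluated are different decisions. A family may be tired of frequent visits and still accept one evaluation at 24 months. The stated pathway does not distinguish the two, and it ends with the family outside the protocol.

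The trigger, the caller and the remedies exist only in the intervention arm, so any outcome loss through this route falls on that arm. The families concerned have disengaged from the programme, and their children may differ in development from those who stay. No control family passes through a comparable filter. At stake is the balance that randomisation gives to the 24-month comparison, which includes the developmental test on which the sample size rests. An analysis plan could state that families are analysed as allocated, but it could not restore evaluations that were never made.

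**Working it through.** **1. The pathway by arm**

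| Step | Intervention | Control |
|---|---|---|
| Programme visits before 24 months | 12 + 6 = 18 | none |
| Dedicated nurse who makes the calls | yes | none mentioned |
| Change of nurse or timetable | can be offered | not applicable |
| Withdrawal after refused visits | possible | not possible by this route |
| Loss to follow-up, refusal, child taken into care | possible | possible |

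**2. The plan's own figures** (Determination of Sample Size: 50% v 25%, power 80%, alpha 5%, 1:1)

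Two-sided test, pooled variance, no continuity correction, mean rate 0.375:

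n = [1.960 × √(2 × 0.375 × 0.625) + 0.842 × √(0.50 × 0.50 + 0.25 × 0.75)]² / 0.25² = 57.7, so 58 per group, as stated.

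The 10% allowance gives 58 × 1.10 = 63.8, so 64, as stated (58 / 0.90 = 64.4 would round up to 65). These figures are not in dispute. The allowance is a single figure, not split by arm.

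**3. Illustration of the bias**

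Assume no true effect and 50% delay in both full arms. Let w be the share of intervention families withdrawn by this route and p the share of their children with delay. Neither is in the documents; both are assumptions.

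Prevalence among retained intervention families = (0.50 − w × p) / (1 − w). The apparent benefit is 0.50 minus that.

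| w | p | Retained prevalence | Apparent benefit (points) | Two-sided type I error |
|---|---|---|---|---|
| 10% | 50% | 50.0% | 0 | 0.050 |
| 10% | 60% | 48.9% | 1.1 | 0.052 |
| 10% | 70% | 47.8% | 2.2 | 0.057 |
| 10% | 80% | 46.7% | 3.3 | 0.066 |
| 20% | 50% | 50.0% | 0 | 0.050 |
| 20% | 60% | 47.5% | 2.5 | 0.058 |
| 20% | 70% | 45.0% | 5.0 | 0.083 |
| 20% | 80% | 42.5% | 7.5 | 0.125 |

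The error rates take all 64 controls as evaluated, with 58 (w = 10%) or 51 (w = 20%) intervention families retained. The largest entry is 7.5 / 25 = 30% of the planned effect.

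The sign depends on p. With w = 20% and p = 40%, retained prevalence is (0.50 − 0.08) / 0.80 = 52.5%, an apparent harm of 2.5 points.

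**4. What keeping these families does to power**

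Suppose 64 per arm are evaluated, adherent families have 25% delay and families who stop have the control rate of 50%. The intervention rate is then (1 − w) × 25% + w × 50%: 27.5% at w = 10% and 30% at w = 20%. Power is 0.749 and 0.639 respectively, against 0.840 with the full 25-point effect at 64 per arm.

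**The case against.** The strongest reply is that the sentence records families who choose to leave. Withdrawal is not automatic: it follows three calls, a call from the coordinator and an offer of adjustments, and that call is described as asking why the parents want to leave the study. The article nowhere says that a family declining visits but willing to be evaluated would be turned away. This stands in part. Some of these families will have withdrawn consent, and that must be respected. But the sequence begins with missed visits, the remedies named are all about visits, and the option to stop visits and keep the evaluation is absent.

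A reader might infer that the 24-month comparison becomes adherent intervention families against all controls, in effect a per-protocol analysis in one arm. The documents do not support that. No minimum number of visits is set, and a family that answers the nurse or accepts another timetable stays in, so partial adherers are retained. Controls can also be lost or refuse, and the section foresees controls leaving before the 4-month visit. No per-protocol analysis is stated.

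Three other strong readings also fail. The 4-year language result is not necessarily lost, because the screen is done in schools. Drawing on the 10% allowance is not a fault, because the allowance exists for losses. And the bias need not favour the intervention: its size and direction rest on assumed values, and 20% withdrawn in one arm is twice the planned overall loss.

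**Conclusion.** The point holds as a weakness in a stated conduct rule. The article treats persistent refusal of nurse visits as leaving the study, offers no route that keeps the 24-month evaluation, and applies this where visits exist, in the intervention arm. Arm-specific, engagement-related loss of 24-month outcomes is therefore possible; the documents do not show that it has occurred.

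Under the assumptions shown, the spurious benefit is about 1 to 7.5 points. At a withdrawn share equal to the plan's own 10% allowance it is 1.1 to 3.3 points, with type I error of 0.052 to 0.066. It is zero if stopping is unrelated to outcome and reverses if withdrawn children do better. This is an inexpensive improvement that protects the randomised comparison, not a proven defect in the results. It concerns mainly the 24-month outcomes.

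**What to change.** Amend Data Collection to separate two events: stopping the nurse visits, and leaving the study. How visits are managed or ended need not change.

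- A family that stops visits stays in its allocated group and is still offered the 24-month evaluation. Its school ERTL-4 result is used. Both apply unless the family explicitly refuses evaluation or withdraws consent.
- These families are analysed as allocated, whatever number of visits they received.
- Losses are reported by arm and by reason, with stopped visits, refused evaluation and withdrawn consent kept apart.
- For families already withdrawn under the present wording, the 24-month evaluation is offered only where the record shows that they declined visits and did not withdraw consent to the research.

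The cost is a few evaluation visits and an application to the ethics committee, which the Ethical Principles and Safety section requires for any protocol change. Including families who stopped visits may also shrink the observed effect and lower power, as the working shows.
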